### Recruitment

#### Sample size

According to CONSORT guidelines, sample size calculations are based on adequate power for comparison between the effects of the *Sports Stars* program compared to standard care using the COPM immediately post intervention (T2). Data from a previous study investigating the effects of an exercise group aiming to improve physical activity, balance and strength in ambulant children with CP (6–14 years) showed a standard deviation of 1.87/2.88 (intervention/control) [32]. This standard deviation and a mean change of 2 points for performance on the COPM (clinically meaningful difference) were used to calculate sample size. Based on significance (alpha) of 0.05 and 80% power, a minimum sample of 25 participants in each group (50 participants total) will be required. Therefore, 60 participants (30 in each group) will be recruited to allow for 20% attrition.

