#### Recruitment process

Eligible children will be prospectively recruited through the client database of a state-wide community rehabilitation service. As geographical location and participant availability are critical to forming groups of sufficient participant numbers for this study, participants will be recruited in blocks according to their geographical location. Once at least four, and a maximum of six, children are identified that can attend an eight-week group on a specified day in a specific geographical location, these children will be assigned as group one. When a second group of four to six children are identified for a geographical location, they will be assigned as group two. When two groups of four to six participants each are identified, they will proceed to randomisation.

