#### Randomisation

A random sequence will be generated via coin flip by an independent, off-site co-investigator (MA) who will not be involved with assessment or treatment (as per process used in previous studies [17]). The outcome (heads: group 1 = immediate *Sports Stars* intervention, group 2 = waitlist *Sports Stars* intervention. Tails: group 1 = waitlist *Sports Stars* intervention, group 2 = immediate *Sports Stars* intervention) will be written on a piece of paper and concealed inside a sequentially numbered, opaque envelope and stored securely off-site.

When two groups are identified, they will be randomly assigned to either the immediate intervention group or the waitlist control group with a 1:1 block allocation via drawing of one of the opaque envelopes. Randomisation will be completed offsite by the same independent co-investigator (MA). This process will continue until 60 participants complete baseline assessments and proceed to the *Sports Stars* group.

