#### Sports Stars intervention

Each group will contain between four and six participants with one lead Physiotherapist. The immediate *Sports Stars* group will receive eight, one-hour, weekly sessions (8 hours) of group-based, sports specific fundamental movement skills training, detailed in Fig. 3. These groups will introduce children to four popular Australian sports and support the development of core motor skills for transition to recreational mainstream and modified sports opportunities including *Junior Entry Point* sports programs, NetSetGo (netball), In2Cricket, MiniRoos (soccer) or T-Ball (softball/baseball). To achieve this, *Sports Stars* will focus on developing key *Body Functions* (aerobic and anaerobic fitness, muscle strength, balance and agility, and locomotor and object control) and sport-specific *Activity* skills to facilitate participation in modified sport games of soccer, netball, T-ball and cricket.

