## Analyses

Statistical analysis will be performed using SPSS statistical software. Primary analysis will use the intention to treat principle, using the last observation recorded for participants who withdraw from the program.

Baseline data will be reported using descriptive statistics for each variable (individual sports related activity and participation goals, GM capacity, aerobic fitness, anaerobic fitness and agility, functional strength, participation and quality of life) to establish any difference between randomised groups. The method of aggregation will depend on the normality of the data and will include the mean and standard deviation (normally distributed data) or the median and interquartile range (non-normally distributed data). If characteristics are not comparable at baseline, they will be modelled as covariates in subsequent analyses in order to adjust their possible confounding effects. Linear mixed models will be used to evaluate the effectiveness of the *Sports Stars* intervention compared to the waitlist control on the primary outcome (COPM). Linear mixed models take into account variation in individuals over time, are able to manage missing data without excluding participants for further analysis and examine changes in the outcomes over time as well as across the two groups. Significance will be set at *p* < 0.05. Residuals of the fitted models will be examined to ensure that all required assumptions are met.

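### Whole therapy groups are randomised in location pairs, but the COPM mixed model as described and the sample size treat children as independent

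*Protocol article*

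**What the plan says.** Recruitment process (Protocol article): "participants will be recruited in blocks according to their geographical location". Children who can attend on the same day in the same area are assembled into a group, and a second group is assembled for that area. Then: "When two groups of four to six participants each are identified, they will proceed to randomisation".

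Randomisation: "When two groups are identified, they will be randomly assigned to either the immediate intervention group or the waitlist control group". One coin-flip result in one envelope settles both groups of the pair. No child is allocated individually.

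Sports Stars intervention: "Each group will contain between four and six participants with one lead Physiotherapist".

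Sample size: "Based on significance (alpha) of 0.05 and 80% power, a minimum sample of 25 participants in each group". The inputs are a COPM difference of 2 points and standard deviations of 1.87 and 2.88. No ICC or design effect is given, and 60 children are to be recruited.

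Analyses: linear mixed models are named for COPM, with the rationale that "Linear mixed models take into account variation in individuals over time", that they cope with missing data, and that they examine change over time and between the two arms. Neither this section nor any other mentions therapy group, therapist, location or pair as a model term, or a cluster-robust variance. Study aims describes the trial only as having two parallel groups.

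**The concern.** The unit that chance assigns is the therapy group, within a location pair. The dependence that the described model addresses is repeated measurement within a child. A treated group shares one physiotherapist, the same peers and the same eight sessions, which include games played together. Outcomes within it may therefore be more alike than outcomes of children in different groups. A model without a group term would count that shared variation as independent information. The standard error of the arm contrast would be too small, and a superiority claim on the primary outcome would carry more than the nominal 5% risk of being false. Power is also affected: a valid analysis has only about 10–16 randomised units behind it, whereas the sample size was worked out for 50 independent children.

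**Working it through.** **1. Number of randomised units.** A pair holds 8 to 12 children. 60/12 = 5 pairs and 60/8 = 7.5, so there are 5–8 pairs, or about 10–16 groups.

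**2. The plan's own figure.** Pooled SD = sqrt((1.87² + 2.88²)/2) = 2.428. With a difference of 2, two-sided alpha 0.05 (sidedness is not stated) and 80% power, the normal formula gives 23.14, so 24 per arm. The noncentral t gives 25 per arm (power 81.4%; 79.8% at 24). The stated 25 is therefore reproduced with independent children and no design effect.

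**3. Type I error if group is ignored.** The documents give no group-level ICC; the ICCs in the outcome sections are reliability coefficients and do not apply here. A range is assumed, with group size m = 5, the midpoint of four to six.

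- Both arms clustered: the variance of the contrast is inflated by DE = 1 + (m − 1) × ICC.
- Only the treated arm clustered: with equal arms the inflation is V = (DE + 1)/2.
- True type I error = 2 × (1 − Φ(1.96/√inflation)).

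The simulation used six pairs of groups of five, 40,000 runs per setting, with a child-level t test standing in for the T2 contrast.

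| ICC | DE | Both arms: formula / simulation | V | Treated arm only: formula / simulation |
|---|---|---|---|---|
| 0.02 | 1.08 | 5.9% / 5.9% | 1.04 | 5.5% / not run |
| 0.05 | 1.20 | 7.4% / 7.5% | 1.10 | 6.2% / 6.0% |
| 0.10 | 1.40 | 9.8% / 9.7% | 1.20 | 7.4% / 7.4% |
| 0.20 | 1.80 | 14.4% / 14.6% | 1.40 | 9.8% / 9.8% |

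For both arms clustered at ICC 0.20, groups of four to six give 12.1% to 16.6%. A t test on group means stayed at about 5% in all the both-arm and treated-arm settings.

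**4. Location.** Both groups of a pair come from one location, so a location effect cancels in the contrast. With location variance alone (5% or 10% of the total), the child-level test rejected in 4.6% and 4.0% of runs, which is slightly conservative. With location and group variance together, the rates were 6.9% (0.05 each) and 9.2% (0.10 each).

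**5. Power of a valid analysis.** Take 25 analysed per arm, six groups per arm, both arms clustered, and a t reference with 2 × (6 − 1) = 10 degrees of freedom. The noncentrality is 2/(2.428 × sqrt(2 × DE/25)). Power is about 72%, 67%, 60% and 50% at ICC 0.02, 0.05, 0.10 and 0.20. At ICC 0.01 it is still only 73%, so much of the shortfall from 81% comes from having few groups. These figures take no credit for variance removed by the pairing. They also keep m = 5, although 25 analysed in six groups is about 4.2 per group, so the design effect is slightly overstated.

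**The case against.** The strongest reply is that the sentence in the Analyses section is a general argument for mixed models and not a list of random effects. An article may leave that list to a fuller plan, and a mixed model can hold a group term. This is fair as far as it goes: the article does not rule a group term out. But it sets out the allocation procedure, the sample-size inputs and the reason for choosing the model, and both the reason and the sample size take the child as the unit. The stated analysis does not match the stated randomisation.

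Other objections stand and limit the point:

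- A reader might infer that type I error is known to exceed 5%. The documents do not establish that. It requires both an omitted group term and positive within-group correlation beyond what the paired groups share, and no ICC is given.
- A reader might count shared place and calendar time as sources of false positives. Location is common to the pair, and T1 to T3 are timed for everyone around the immediate intervention, so calendar time is largely common too. Leaving out the pair costs efficiency; it does not inflate error.
- Waitlist children receive standard care, typically one to one, and have no shared Sports Stars sessions before T3. The treated-arm-only column may therefore be closer to the truth, although some similarity among waitlist children grouped together is possible.
- The mixed model is specified for COPM only. For secondary outcomes the problem arises if they too are compared at child level.
- With five pairs, an exact randomisation test could not give a two-sided p-value below 2/2⁵ = 0.0625. A reader might conclude that the trial cannot reach significance. No such test is planned, and five pairs arise only if every group has six children.

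**Conclusion.** The point holds in conditional form. Allocation is by therapy group within location pairs, while the described COPM model and the sample size treat children as independent. If there is within-group correlation beyond that shared by the pair, the planned test is liberal. With groups of five and ICCs of 0.05, 0.10 and 0.20, true type I error is about 6%, 7% and 10% with clustering in the treated arm only, and about 7%, 10% and 14–15% with equal clustering in both arms. These ICCs are assumptions. The mismatch between unit of randomisation and analysis is in the text whatever their value. It affects the validity of the primary superiority test and should be settled before analysis.

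**What to change.** In the Analyses section:

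- Add a random intercept for therapy group as randomised. As a sensitivity analysis, let its variance differ by arm or apply it to the treated arm only.
- Include location pair as the randomisation stratum.
- Use Satterthwaite or Kenward–Roger degrees of freedom.
- Report the estimated group-level ICC.
- Use the same structure for every secondary outcome compared between arms.

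In Study aims and the Abstract, describe the trial as randomised by therapy group. In Sample size, state that the 80% power assumes no clustering, and give the power under stated ICCs: about 72%, 67% and 60% at 0.02, 0.05 and 0.10, on the assumptions above.

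No new data are needed, since group and location are recorded by design. The cost is precision. With pair as stratum and 5–8 pairs, about 4 to 7 degrees of freedom remain for the arm contrast. The critical t is then about 2.78 to 2.36 instead of 2.00, so intervals are 18–39% wider (2.36/2.00 = 1.18; 2.78/2.00 = 1.39) before any design effect. Removing location variance may recover part of this. The power figures above use a more generous 10 degrees of freedom.

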## Discussion

This protocol paper presents the background and design of a randomised controlled trial designed to investigate the effectiveness of delivering sports-focussed fundamental motor skills therapy, *Sports Stars,* for children with CP through a group-based service model compared to standard care. To our knowledge this will be the first study of its kind to investigate a culturally relevant sports-based physiotherapy group in this population in Australia. It will add to a growing body of evidence supporting group therapy for children with CP and provide an avenue for children to transition from individual therapy to participating in junior entry-level sport programs such as MiniRoos, NetSetGo, T-Ball and in2Cricket, and onto recreational and competitive mainstream and modified sport. This study will encourage therapy providers to engage with flexible service delivery in response to client and family preferences and goals, and inform parents and carers in deciding how to allocate their funding.

## Abbreviations

CAPE-PAC: Children’s assessment of participation and enjoyment and preferences of activities for children
COPM: Canadian occupational performance measure
CP QoL-child: Cerebral palsy quality of life- children’s version.
CP: Cerebral palsy
CPL: The Cerebral Palsy League of Queensland
FMS: Functional mobility scale
GC: [name]
GMFCS- E&R: Gross motor function classification system- extended and revised
GMFM Challenge: Gross motor function measure- challenge module)
ICC: Intraclass correlation coefficient
ICF: International classification of functioning, disability and health (ICF)
LJ: [name]
MA: [name]
MPST: Muscle power sprint test
T1: Time one
T2: Time two
T3: Time three
T4: Time four
TGMD-2: Test of gross motor development- version two
TUG: Timed up and go
